### Intervention

The Health-Action Process Approach (HAPA) will be used as a theoretical framework to develop the intervention [52,53]. The HAPA Model distinguishes two phases during the process of behavior change: a motivational phase in which the intention to perform a specific behavior is formed and a volitional phase in which the intention is translated into the actual performance of the behavior. Depending on the stage, people have different needs. Within the motivational phase positive outcome expectancies, a high risk perception and a high self-efficacy to perform the specific behavior are necessary to develop an intention. Once people have formed the intention to perform a certain behavior, skills such as action and coping planning, self-efficacy, and social support are necessary. The HAPA Model further distinguishes between stages of intention. Non-intenders are in the motivational phase and have no intention to change their behavior. Intenders are in the volitional phase but do not perform the behavior in contrast to actors, who carry out the behavior [52]. The intervention will target the concepts of the different stages via the use of behavior change techniques. In line with Abraham and Michie [54], we use several behavior change techniques like providing information about behavioral risk and benefit of behavior change, prompting intention formation, prompting barrier identification, providing instructions how to perform a behavior, prompting specific goal setting and review of behavioral goals, providing feedback on performance, prompting practice and providing follow-up prompts, prompting to plan social support and finally prompting relapse prevention, also based on strategies used by other effective computer tailoring programs [55,56].

During the eight-week intervention period, participants will be invited to access the online program once per week and take part in one of the intervention modules. These eight modules aim to increase participants´ risk perception of CVD, support positive outcome expectancies towards physical activity and fruit and vegetable consumption, and guide participants in defining and reflecting on their own goals, action plans and coping plans. Further, self-efficacy regarding the participant’s ability to perform and maintain the two targeted behaviors will be addressed.

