Normative feedback will be provided to give information about whether the behavior meets the recommendations for both target behaviors [42,56]. Feedback will not only be based on the assessment at the beginning of the intervention T1 but also given dynamically with the use of information that will be assessed during the intervention. In this way the feedback is based on the newest information and contains more relevant information. *“Ben, you ate 3 portions of fruit and vegetable per day. This is a bit more than the last time. Great! But remember, it would be good for you to eat at least 5 portions fruit and vegetable a day. RENATA can support you to achieve this goal.”* In addition, a figure (see Figure 1) will present the prior behavior, the behavior of the past weeks, and whether participants fulfill the recommended amount of physical activity or fruit and vegetable consumption.

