### Past health behavior

The level of physical activity will be assessed with the use of the short version of the International Physical Activity Questionnaire (IPAQ) [62]. Participants will be asked to estimate how many days during the past seven day they were vigorous and moderate physically active. Further, the amount of days and spend time for walking during the past seven days will be asked. The IPAQ is a valid measurement instrument which allows an international comparison of participant’s physical activity level.

To assess the fruit and vegetable consumption during the past seven days, four items will be used. Participants will be asked to count the number of consumed portions or glasses fruit and vegetable a day. It will be distinguished between fruit, fruit juice/vegetable juice, cooked or steamed vegetable, and salad and raw vegetable [63].

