### Main study outcomes

The primary study parameter of this study is to analyze the effectiveness of a rehabilitation aftercare program with regard to the level of physical activity and fruit and vegetable intake. The effect of the program will be compared between the intervention group and the control group as well as between the different countries. Secondary study parameters that will be investigated are self-efficacy, outcome expectations, habit, compensatory cognitions, social support, action and coping planning, intention to change, duration absence from work, quality of life and wellbeing. The other study parameters which will be considered are demographic variables, socioeconomic status, stage, age, gender, depression, and health status.

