### Statistical analysis

Descriptive statistics will be used to describe baseline characteristics of the study. We will assess whether there are significant differences between the intervention group in comparison with the control group according to physical activity and nutrition by means of linear regression analysis in PASW (SPSS). The pre-test and post-test measurements of the control group will be compared with the measurements of the intervention and controle group with regard to the target behaviours.

To be able to assess the impact of the intervention on the performance of physical activity and fruit and vegetable consumption, we intend to perform several analyses of covariance (ANCOVA) after four weeks (T3) and six months (T4), controlling for the baseline performance. Multivariate regression analysis will be used to determine possible confounding or modification effects. Regression analysis will allow us to identify the percentage of variability of the dependent variable that is explained by the determinants used. In order to detect differences between the study condition and the control group, effect sizes will be calculated for each study group separately [78].

Subgroup analyses will be performed to determine if the benefit of the intervention depends between groups like nationality or socioeconomic status [79]. Further, dose–response-analyses will be conducted with logistic regression to see if the intervention effect depended on the time spent on the webpage.

Baseline characteristics of participants who dropped out will be compared with participants who finished the intervention to examine whether drop out is at random or determined by specific characteristics.

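### The planned dose-response analysis can show only an association between self-chosen webpage time and outcome, not that the randomised effect depends on dose, and its logistic model discards information

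*Protocol article*

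**What the plan says.** Three parts of the protocol article bear on this.

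- **Dose-response (Statistical analysis).** The analyses "will be conducted with logistic regression to see if the intervention effect depended on the time spent on the webpage". The sentence names the model, the exposure and the conclusion sought. It does not name the binary outcome, the participants included, any adjustment or a time point.
- **Outcomes.** Main study outcomes defines effectiveness "with regard to the level of physical activity and fruit and vegetable intake". Past health behavior measures activity with the IPAQ short form, and for diet: "Participants will be asked to count the number of consumed portions or glasses fruit and vegetable a day". Statistical analysis otherwise treats these as continuous, by linear regression and by "several analyses of covariance (ANCOVA) after four weeks (T3) and six months (T4), controlling for the baseline performance".
- **How use arises.** Under Intervention, "participants will be invited to access the online program once per week and take part in one of the intervention modules". No amount of use is assigned. Under Study design, the waiting list group has no access until its second measurement has been taken.

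**The concern.** Asking whether the intervention effect depends on something is a question about effect modification. It is answered by comparing the randomised contrast across levels of a variable fixed before randomisation. Time on the page is not such a variable: it arises after randomisation and the participant decides it. Motivation, computer skill and reading speed can all influence it, and motivation also influences activity and diet. The Health Action Process Approach described under Intervention gives intention and self-efficacy a central role in behaviour, and the same traits plausibly drive use of the site.

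Taken as written, the analysis could report that the effect depends on dose when all it has found is that more motivated people both log in longer and behave more healthily. Separately, a logistic model needs a yes/no outcome, so it discards information that the continuous measures hold.

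**Working it through.** **1. What contrast is available.** Until the second measurement, webpage time varies in the intervention arm and is zero for every control. No control has a comparable value, so the randomised difference cannot be estimated at different amounts of time. Only a within-arm, non-randomised association remains. At the ANCOVA time points (T3 and T4), Table 1 has the waiting list group already started on the programme. Time then accrues in both arms, again by choice, so pooling the arms does not restore a randomised comparison.

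**2. Information kept after dichotomising.** For a normal outcome and a small association, the efficiency relative to the continuous analysis is φ(z)² / [p(1 − p)], where p is the share above the cut-off and z the corresponding normal quantile.

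- Median split, p = 0.5: z = 0, φ = 0.3989; 0.1592 / 0.25 = 0.637.
- 80/20 split, p = 0.2: z = 0.842, φ = 0.2800; 0.0784 / 0.16 = 0.490.

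For this test, 263 users are worth about 263 × 0.637 = 167 or 263 × 0.490 = 129 users analysed on the continuous scale.

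**3. False dose-response when use has no causal effect.**

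Inputs from the article (Power analysis): 263 per group per country, so 263 intervention users in one country and 2 × 263 = 526 in both, before dropout; alpha 0.05, taken as two-sided.

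Assumed, because the article gives no figure: a correlation r between use and the normally distributed outcome, arising only from a shared cause. The range 0 to 0.2 is shown.

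Method: dichotomising shrinks r to r′ = r × √efficiency, that is r × 0.798 (median split) or r × 0.700 (80/20). The test statistic is then centred at about atanh(r′) × √(n − 3), and the chance of significance is Φ(centre − 1.96), plus a small opposite tail.

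Example: r = 0.2, n = 263, median split. r′ = 0.160; centre = 0.161 × 16.12 = 2.60; Φ(0.64) = 0.74.

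| n | r | Median split | 80/20 split |
|---|---|---|---|
| 263 | 0 | 5% | 5% |
| 263 | 0.05 | 10% | 9% |
| 263 | 0.1 | 25% | 20% |
| 263 | 0.2 | 74% | 62% |
| 526 | 0.1 | 45% | 36% |
| 526 | 0.2 | 96% | 90% |

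Simulating the logistic model itself (4,000 trials per setting) agrees to within about one percentage point. For r = 0.2 it gives 74% and 63% at 263 users, and 96% and 89% at 526.

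**4. The same check on a linear model.** Without dichotomising, r is not shrunk. At r = 0.2 and n = 263 the centre is 0.203 × 16.12 = 3.27, which gives 90%; at n = 526 the rate exceeds 99%. These higher rates belong to a linear test and should not be quoted against the logistic model that the article plans.

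**The case against.** The strongest reply has four parts.

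- **The cut-off is detail for another document.** This is a condensed article, and a cut-off for one supplementary analysis commonly sits in the full protocol or analysis plan. This stands. A reader might infer that logistic regression is impossible here or contradicts the outcomes. The documents do not support that. Natural thresholds (5 portions a day; 5 days of 30 minutes) run through the feedback and questionnaire items, and the Intervention section says: "Normative feedback will be provided to give information about whether the behavior meets the recommendations for both target behaviors". A continuous main analysis can coexist with a binary secondary one. What remains is the loss of information.
- **Controls may not enter the model.** The article does not say that they do, and a within-arm analysis is an ordinary reading. That is fair, but a within-arm analysis has no randomised contrast at all, so the conclusion sought is still out of reach.
- **The harm is speculative.** A reader might infer that a dose-response result would be used to claim efficacy after a null randomised comparison. Nothing in the article says so. Impact is to be judged by ANCOVA, and the stated hypothesis in the Discussion compares intervention with control. The error rates also rest on an assumed correlation, and at 0.05 with 263 users they are only about 9 to 10%.
- **Linear regression has the same confounding.** This also stands: step 4 shows that the more efficient model detects a spurious association more often. Changing the model recovers information; only adjustment and honest wording address the inference.

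**Conclusion.** The point holds, and it is minor. The sentence assigns to a non-randomised comparison a conclusion about the randomised effect that it cannot deliver. That follows from how use arises and needs no numerical assumption.

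The sizes are illustrative. The 64% and 49% assume a normal outcome and a small association; portion counts and activity time may well be skewed, and the loss would then differ. The false-positive rates assume that use has no causal effect, that the correlation takes the stated values after any adjustment, and that there is no dropout. With 263 users they run from about 9% at r = 0.05 to about 74% at r = 0.2.

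The analysis is supplementary. The ANCOVA of activity and of fruit and vegetable intake does not depend on it.

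**What to change.** - **Model.** Within the intervention arm, use linear regression of the continuous outcome on time on the page (or modules completed). Adjust for the baseline value of the outcome, intention, self-efficacy, stage, education and age. The article already lists measures of all of these.
- **Wording.** Replace the statement that the intervention effect depended on time with one that the outcome *is associated with* time, and label the analysis exploratory and observational.
- **If a logistic model is kept** as a secondary presentation, base it on the recommendations already used in the programme: 5 portions a day, and 5 days of 30 minutes.
- **Do not offer two-stage least squares as the answer to the dose question.** With randomisation as a single binary instrument, it only rescales the randomised contrast by the difference in use. It cannot test whether the effect varies with dose, and it needs an exclusion assumption as well.

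The cost is a change of wording and a little more analysis, with no new data on the covariates. The claim becomes weaker, and residual confounding remains that adjustment cannot exclude.

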## Discussion

The results of this study are important for the future development of online-based rehabilitation aftercare programs for cardiovascular patients and the development of online interventions in general. Although there is no doubt about the positive effect of adequate physical activity and fruit and vegetable consumption for people undergoing rehabilitation [8,11,13,17,22,80], many patients fail to maintain lifestyle changes [26-28]. To transfer the rehabilitation results into the daily life and to overcome unhealthy habits, effective rehabilitation aftercare is necessary.

Given the benefit of tailored health behavior change interventions, there is still a need for further research. It is important to develop guidelines for interventions which are effective in different countries with different rehabilitation systems. In order to make a positive contribution, an international implementation and evaluation of this study will be done within Germany and the Netherlands.

It will be assessed to what extent the health status, quality of life and return to the labor market can be realized among the participants. Our hypothesis is that participants in the intervention group will increase their level of physical activity, fruit and vegetable consumption and are able to maintain these behaviors over a longer period of time compared to the control group.
